### Provision for post-trial care

Upon completion of the trial, participants who have derived benefits from the intervention and continue to require it will be ensured ongoing access to the intervention. Moreover, if participants in the control group demonstrate a need for the intervention during the study’s duration, they will be offered the chance to receive it.

## Outcomes

### Primary outcome

The primary outcome in this trial is Wexner score, a widely recognized assessment tool extensively employed in clinical practice to assess bowel dysfunction [21]. The Wexner score encompasses both constipation and fecal incontinence scales. The constipation scale comprises 8 items: frequency of defecation, difficulty, completeness, pain assessment, duration of defecation (in minutes), assisted defecation, number of unsuccessful defecations attempts per 24 h, and duration of constipation (in years). The rating of assisted defecation follows a scale of 0–2, while the other items are graded on a scale of 0–4, representing a range from mild to severe [22]. The overall score ranges from 0 to 30, with higher scores indicating greater severity of constipation symptoms.

The Wexner incontinence scale assesses the frequency of gas, liquid, and solid incontinence, in addition to the utilization of pads and lifestyle adjustments [23]. The total score ranges from 0 to 20, with higher scores correlating to increased severity. Item scores vary from 0 to 4, where 0 signifies “never” and 4 signifies “always.” A score of 1 signifies occasional incontinence, while a score of 2 denotes “sometimes,” and a score of 3 indicates “often.”

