#### Sample size

The sample size calculation was performed using the PASS15 software, Version 15.0.5, with reference to a prior randomized controlled trial conducted in China that reported the Wexner score as the primary outcome [27]. We selected a significance level of 0.05 and a power of 90%. Assumptions encompassed an equal allocation of participants in a 1:1 ratio between two groups and a 20% dropout rate. The mean for group 1 (μ_1_) was 10.65, and group 2 (μ_2_) was 9.10. The standard deviation for group 1 (σ_1_) was 2.08, and for group 2 (σ2), it was 1.73. The anticipated effect size was 0.81. The sample size calculation indicated that each group should comprise 40 patients.

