## Assignment of interventions

### Allocation—sequence generation

Participants will first be stratified into two groups based on their baseline National Institutes of Health Stroke Scale (NIHSS) scores: one group with scores ranging from 0 to 4 and the other group with scores ranging from 5 to 15. Participants will then randomly be assigned in a 1:1 ratio to either the intervention or control arm. Random numbers within the range of 0 to 1 will be generated using the SPSS 25.0 software by an independent statistician and subsequently ranked. The allocation of participants will be determined based on the ranking of the generated random numbers. For the group with NHISS scores ranging from 0 to 4, odd-ranked numbers will be allocated to the intervention group, while even-ranked numbers will be assigned to the control group. Conversely, in the range of 5 to 15, this allocation will be reversed.

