### Statistical analyses

The collected data will undergo analysis using IBM SPSS Statistics 25.0 (IBM Corp., Armonk, NY, USA). Baseline characteristics will be summarized using descriptive statistics. Continuous variables, such as the Wexner score and quality of life score, will be reported using means, medians, standard deviations, and score ranges. Categorical valuable, such as BSFS, will be reported as counts and percentages. To ascertain normality, the Kolmogorov-Smirnova test will be applied. In instances of normally distributed data, independent samples *t*-test will be employed to compare efficacy between the intervention and control groups in terms of the Wexner score, PAC-QoL, and FI-QoL. Non-normally distributed data will be analyzed using the Wilcoxon rank sum test with a test statistic of *Z*. For assessing changes across distinct time points, we will employ repeated measures ANOVA. The chi-squared test will be used to analyze categorical data for the BSFS. A *p*-value < 0.05 will be considered statistically significant. We will perform an intention to treat analysis for participants who either lack adherence to bowel care (defined as comply with less than 80% of bowel care) or discontinue the study. These participants will be retained within their originally randomized treatment arm for analysis. Addressing missing data, a multiple imputation method will be implemented. No supplementary analyses will be carried out in this study, and the study design does not encompass interim analyses.

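### The primary outcome is two Wexner scales with no rule for choosing or combining them, so the 90% power calculated for a single score is not justified for it

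*Protocol article*

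**What the plan says.** All references are to the protocol article.

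- **Primary outcome.** One outcome is named, and then: "The Wexner score encompasses both constipation and fecal incontinence scales". The constipation scale has 8 items and a total of 0 to 30. The incontinence scale has different items and a total of 0 to 20. The Discussion repeats that both scales form the primary outcome.
- **Eligibility criteria.** Constipation and fecal incontinence are each defined as qualifying bowel dysfunction. No expected mix is given.
- **Sample size.** The planning values are a single pair of means (10.65 and 9.10) with a single pair of SDs (2.08 and 1.73), at alpha 0.05 and 90% power, with 1:1 allocation and 20% dropout. The section concludes: "The anticipated effect size was 0.81. The sample size calculation indicated that each group should comprise 40 patients". The figures come from a previous Chinese trial. Which Wexner scale that trial used is not stated.
- **Allocation—sequence generation.** "Participants will first be stratified into two groups based on their baseline National Institutes of Health Stroke Scale (NIHSS) scores". Symptom type is not a stratum.
- **Statistical analyses.** A t-test that "will be employed to compare efficacy between the intervention and control groups in terms of the Wexner score, PAC-QoL, and FI-QoL", with a Wilcoxon test for non-normal data and repeated measures ANOVA for change over time. Significance is set at 0.05. The section has no symptom term and no alpha split, and it rules out supplementary analyses.

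**The concern.** The two totals measure different things on different ranges, but the plan sizes and tests them as one number. Three ways of carrying out the plan fit the text:

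1. each patient is scored on the scale for the qualifying symptom, and each scale is tested in its own group;
2. each patient contributes one total, and the raw totals are pooled in one test;
3. every patient completes both scales, and both are tested.

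The first divides the sample. The second gives a mean difference without a clear unit and adds between-scale variance. The third gives two chances of success at 0.05. Because the text does not choose, the scoring rule could be settled after results are seen. An unseen analysis plan could add a scoring rule, but that would not turn the single pair of planning means and SDs into planning figures for a two-scale outcome.

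**Working it through.** **Inputs from the Sample size section:** means 10.65 and 9.10, SDs 2.08 and 1.73, alpha 0.05, power 90%, dropout 20%, 40 per group. Sidedness is not stated; two-sided is used because the one-sided version gives 27 per arm, or 34 after dropout, and does not reproduce 40.

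**Reproducing the plan's figure**
- Difference = 10.65 − 9.10 = 1.55.
- Pooled SD = √((2.08² + 1.73²)/2) = 1.913.
- Effect size = 1.55/1.913 = 0.810, as stated.
- Normal approximation: n = 2(1.960 + 1.282)²/0.810² = 32.01 per arm; 32.01/0.8 = 40.0.
- Rounding up first gives 33/0.8, or 42. The exact t-test needs 34, or 43 after dropout. These are within 3 of 40, so the stated figure is not an arithmetic error.
- Evaluable per arm = 40 × 0.8 = 32. Power at 32 is 90.0% by the normal approximation and 89.1% by the t-test.

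This holds for one score, with this SD and effect, measured in every patient.

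**Assumptions for the three readings.** The difference of 1.55 and SD of 1.913 apply to each scale, with 32 evaluable per arm. The symptom mix and the gap between scale means are not in the document and are varied. Power is two-sided, from the noncentral t distribution.

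**(a) Each scale tested only in its own symptom group**

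| Assumed mix, constipation:incontinence | n per arm | Power |
|---|---|---|
| 50:50 | 16 and 16 | 60% and 60% |
| 70:30 | 22.4 and 9.6 | about 76% and 39% |
| 80:20 | 25.6 and 6.4 | 81% and 26% |

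**(b) Raw totals pooled, 50:50 mix.** With a gap of D points between scale means and a constipation share p, the SD is √(1.913² + p(1 − p)D²).

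| D | SD | Power at 32 per arm |
|---|---|---|
| 0 | 1.91 | 89% |
| 2 | 2.16 | 81% |
| 3 | 2.43 | 71% |
| 4 | 2.77 | 60% |
| 5 | 3.15 | 49% |

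At an 80:20 mix the loss is smaller: 84%, 77%, 69% and 60% for gaps of 2 to 5.

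**(c) Both scales measured and tested in everyone**
- At 0.05 each: 89% power per scale, but familywise error of 1 − 0.95² = 9.75% if the tests are independent.
- At 0.025 each: 82% power per scale.

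**The case against.** The strongest reply is that every patient may complete both scales. The Primary outcome section restricts neither scale to a symptom group, and the Statistical analyses section lists both quality-of-life instruments without restriction. Each scale then has 32 evaluable per arm and 89% power at 0.05. This stands as a legitimate reading, and it is the mildest for power. The problem then becomes multiplicity, and whether one pair of planning figures suits both scales. The primary variable is still not fixed.

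Stronger inferences that a reader might draw do not hold:

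- **That 90% power is definitely not delivered.** The mix, the scale-specific means and SDs, and the scoring rule are all absent. Power would stay near 90% if nearly all patients were constipated and only that scale were used, or if the two scales shared mean, SD and effect. Even that the planning figures belong to a single scale is inferred from there being only one pair.
- **That symptom type decides which scale a patient is scored on.** This is plausible, but no section says so.
- **That chance imbalance in symptom type creates a false effect.** Randomisation already covers it. Under no effect, a simulated pooled t-test with 32 per arm, a 50:50 mix and a five-point gap rejected 5.1% of the time. The cost is precision, which the table under (b) already counts.
- **That the trial is unstratified.** It is stratified by NIHSS, though not by symptom type.
- **That the Background reports patients with both constipation and incontinence.** Its mention of combined symptoms is not clearly about that pair. The eligibility criteria simply do not exclude overlap.

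It is also fair to say that covariates and the handling of overlap are often left to an analysis plan. Which quantity is the primary outcome, and what the sample size refers to, are stated in this article, and those statements do not fit together.

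**Conclusion.** The concern holds in a limited form: the primary variable is not uniquely defined, and the stated 90% power is not justified for it. The 40 per group is sound for one score in all patients. Each of the three readings has a price: power in (a), interpretability and usually power in (b), type I error control or some power in (c). Under the assumptions above, power ranges from 89% per scale with uncontrolled multiplicity, or 82% per scale with alpha split, down to 60% per scale at a 50:50 mix, 39% for the smaller group at 70:30, and 49% for raw pooling with a five-point gap. These figures show how far the answer depends on what is left open; they are not estimates of this trial's power.

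**What to change.** Before treatment codes are broken:

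1. **Define one primary variable.** For example, use the score on the scale matching the qualifying symptom, standardised within scale, with a fixed rule for patients meeting both definitions. Two co-primary scales with a stated alpha rule would also settle it.
2. **Analyse it in one model** with symptom type, baseline score and NIHSS stratum as covariates. Report scale-specific effects as supportive, and amend the sentence that excludes supplementary analyses to allow this.
3. **Restate the Sample size section.** Name the scale behind the planning figures. Say that about 89–90% power holds only if an effect of 0.81 applies to the defined variable. Give the lower per-scale power under a stated mix.
4. **Optional:** stratify remaining enrolment by symptom type. Lists and envelopes would have to be replaced, and recruitment was due to end around 31 October 2023, so the gain may be small. Covariate adjustment works regardless.

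The cost is a wording amendment, slightly more analysis work and a less favourable stated power. No extra patients are needed unless the sponsor wants 90% power on each symptom group's own scale. That would take 34 evaluable per arm per group: 34/0.8 rounds up to 43 randomised, and 43 × 2 arms × 2 groups = 172 in place of 80.

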Bowel dysfunction is prevalent among stroke patients, with a reported incidence of 55.21% post-stroke and 23.96% in pre-stroke patients [7]. Among patients with bowel dysfunction, 50% take more than 30 min on average to defecate, and 70% require assistance during defecation [8]. Additionally, 15% suffer from chronic bowel dysfunction, leading to potential losses in privacy and intimate relationships and social isolation [9]. This places a significant burden of care on the patient’s family [10]. Currently, clinical caregivers heavily rely on empirical information and predominantly employ single intervention, including conservative strategies such as dietary modifications, bowel irrigation medication, or biofeedback training [11–15]. However, certain medications or enemas have the potential to harm the colonic mucosa and decrease the frequency of colonic peristalsis [16]. Surgical treatment is typically reserved for patients without rectal outlet problems who remain unresponsive to intensive medical and biofeedback therapy [13]. Nevertheless, the limited availability of medical equipment might impede patients’ access to biofeedback treatment. Hence, conservative management is recommended for NBD in stroke patients, prioritizing simple, cost-effective, minimally invasive, and reversible interventions [17].

According to guidelines, DRS is recommended as the first-line intervention and has shown a positive impact on improving bowel dysfunction in patients with spinal cord injuries [1, 18]. Moreover, abdominal massage has proven effective in reducing the severity of bowel dysfunction in elderly stroke patients [19]. The combined intervention of abdominal massage and targeted intestinal peristalsis promotion, along with DRS to facilitate fecal elimination, could potentially yield a significantly enhanced effect. However, the concurrent application of these interventions in stroke patients remains infrequent [1]. Robust evidence regarding bowel management is urgently needed. Consequently, this study aims to assess the effectiveness of a 6-week rehabilitation care program that combines DRS and abdominal massage on both bowel function and quality of life in post-stroke patients. We hypothesize that this comprehensive program will be superior to singular care interventions while minimizing complications.

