## Interventions

### Control group

The participants in the control group will be receive standard care, consisting of dietary guidance, pelvic floor muscle exercises, and skin care. In the event of no enhancement in bowel function over a span of 3 days, prescribed enemas or appropriate medications will be administered as needed.

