### Digital rectal stimulation

The procedure of DRS involves gently inserting either the middle or index finger into the anus. The rectal wall is then gently stimulated in a clockwise direction, creating a circular motion. After completing ten circles, there is a brief pause for 1–2 min. The duration of stimulation is adjusted based on various factors, including the patient’s rectal content, stool consistency, and sphincter muscle strength. The stimulation duration is set at 8 min for mild sphincter injury (anal systolic pressure 15–25 mmHg), 10 min for moderate to severe sphincter injury (anal systolic pressure 0–15 mmHg), and 15 min for severe sphincter injury (anal systolic pressure 0 mmHg). If the patient’s rectal fecal volume exceeds 100 g, the stimulation time is extended accordingly.

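### The Wexner constipation total scores assisted defecation, and only one arm receives digital rectal stimulation by protocol, so allocation itself may shift the primary score at weeks 2 and 6

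*Protocol article*

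**What the plan says.** The Protocol article (Primary outcome) names the Wexner score as primary: "The Wexner score encompasses both constipation and fecal incontinence scales". The constipation scale has eight items. One is assisted defecation: "The rating of assisted defecation follows a scale of 0–2". The other seven run 0–4. On the total: "The overall score ranges from 0 to 30, with higher scores indicating greater severity of constipation symptoms".

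DRS is part of the experimental programme only; the control arm has standard care without it. The Digital rectal stimulation section describes it: "The procedure of DRS involves gently inserting either the middle or index finger into the anus". The Background gives its purpose: "along with DRS to facilitate fecal elimination". The Eligibility criteria list a need for digital help in at least a quarter of bowel movements among the Rome IV features of constipation.

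Standard care, which both arms receive, has its own forms of assistance after 3 days without improvement (Control group): "prescribed enemas or appropriate medications will be administered as needed". Provision for post-trial care also lets control patients who need the intervention receive it during the study.

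Outcomes are collected at baseline, 2, 6 and 12 weeks, and the intervention lasts 6 weeks. The article does not say whether DRS delivered under the protocol counts on the assistance item, and it does not give the item's levels. The Statistical analyses section states that there will be no supplementary analyses.

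**The concern.** The item treats help with defecation as severity. The protocol delivers a form of such help as treatment in one arm, and its own eligibility criteria regard digital help as a sign of constipation. A patient whose bowel function is unchanged could therefore score differently on the primary outcome because of the arm to which he or she was allocated. Blinding the assessor does not remove this, because the item records what was done to the patient.

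The overlap matters most at weeks 2 and 6, during and at the end of the DRS period. If the shift goes against the intervention, a real benefit is diluted and a superiority trial may miss it. If it goes the other way, for instance because DRS does not score but replaces enemas that do, the benefit is overstated. From the total alone, a reader could not tell a change in bowel function from a change in recorded assistance. With supplementary analyses ruled out, nothing planned would show which it was.

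**Working it through.** **Inputs (Protocol article)**
- Item range 0–2; constipation total 0–30, higher is worse (Primary outcome).
- Planned means: "was 10.65, and group 2 (μ_2_) was 9.10". SDs 2.08 and 1.73, significance level 0.05, power 90%, dropout 20%, 40 per group (Sample size).

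**Step 1: reproduce the plan's figures.**
- Difference: 10.65 − 9.10 = 1.55.
- Pooled SD: √((2.08² + 1.73²)/2) = √((4.3264 + 2.9929)/2) = 1.913.
- Effect size: 1.55/1.913 = 0.81, as stated.
- Normal approximation, two-sided 0.05, 90% power: n = 2 × (1.960 + 1.282)² × 1.913² / 1.55² = 32.01, rounded up to 33 per arm. Then 33 × 1.2 = 39.6, i.e. 40, as stated. (Dividing by 0.8 gives 42.)

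With 40 randomised and 20% lost, 40 × 0.8 = 32 per arm remain.

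**Step 2: how far the item could move the comparison.** The most one patient can gain on it is 2 points. The between-arm shift is the intervention mean minus the control mean on the item. If every intervention patient scored 2:

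| Control mean on item | Net shift | Visible difference (1.55 − shift) |
|---|---|---|
| 0 | 2.0 | −0.45 |
| 0.5 | 1.5 | 0.05 |
| 1.0 | 1.0 | 0.55 |
| 1.5 | 0.5 | 1.05 |
| 2.0 | 0 | 1.55 |

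The shift exceeds 1.55 only if it is more than 1.55/2 = 77.5% of the item's range. Here that means a control mean below 2 − 1.55 = 0.45.

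A negative shift is also possible. If controls collected 0.5 more points on the item, a true 1.55 on the rest of the scale would appear as 1.55 + 0.5 = 2.05.

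**Step 3: effect on power for assumed net shifts against the intervention.** Unequal-variance t-test, two-sided 0.05, SE = √((2.08² + 1.73²)/n). This is 0.478 at n = 32 and 0.428 at n = 40. Power is the probability of rejecting in favour of the intervention.

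| Net shift | Visible difference | Power, 32 per arm | Power, 40 per arm |
|---|---|---|---|
| 0 | 1.55 | 89% | 95% |
| 0.25 | 1.30 | 76% | 85% |
| 0.5 | 1.05 | 58% | 68% |
| 1.0 | 0.55 | 20% | 24% |

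The 40-per-arm column fits an analysis of everyone randomised if imputation lost no information; the 32-per-arm column fits completers after 20% dropout. Both columns assume that every analysed patient is on the constipation scale, that 1.55 is a constipation-scale difference with no such shift already in it, and that the SDs are unchanged. The shifts are assumed values; the article gives no basis for choosing among them.

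**The case against.** The strongest objection is that the premise cannot be confirmed from the article. The item's levels come from a cited source, and DRS is described as circular stimulation of the rectal wall, with no frequency given. Whether it scores, at what level and for what share of bowel movements is unknown. A condensed article may also leave scoring conventions to the full protocol. This stands, so the point is conditional. But the exclusion of supplementary analyses is stated, not left out, and it closes the simplest check.

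A reader might infer that the intervention raises its own primary outcome by more than the planned effect. The documents do not support that. It compares one patient's maximum on an item with a difference between group means, and it needs the near-extreme case in Step 2. Enemas, medication, digital help already needed at entry and control access to DRS all narrow the gap.

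Nor can one say that the bias runs against the programme. If DRS reduces enema or medication use and scores no higher than they do, the item favours the intervention.

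A reader might also expect an artificial improvement from week 6 to week 12 when DRS stops. The article does not say that it stops for everyone: it promises continued access after the trial to those who benefit, and does not say when that begins.

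Finally, the Sample size section does not say whether 1.55 is on the constipation or the incontinence scale. The incontinence scale lacks this item, and patients with incontinence are also enrolled.

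Using a standard scale whole is defensible, so replacing the primary score is not warranted.

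**Conclusion.** The point holds in conditional form. The primary constipation total includes an assistance item, one arm receives a manual aid to emptying by protocol, and nothing in the article separates the two. If delivered DRS counts as assistance, allocation can shift the week-2 and week-6 constipation scores by up to 2 points, against a planned 1.55 if that is a constipation-scale figure. The actual net shift and its direction are unknown.

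A shift well short of the maximum would matter. A net 0.5, a quarter of the item's range, would hide 0.5/1.55 = 32% of the planned difference and leave 58% power at 32 per arm or 68% at 40, under the assumptions in the working. The incontinence scale is unaffected. This justifies a prespecified check, not a new primary outcome or a new sample size.

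**What to change.** - Prespecify, as a sensitivity analysis, the 7-item constipation total without assisted defecation (7 × 4 = 28, so 0–28). Derive it identically in both arms and report it beside the full 0–30 total, which stays primary.
- Report the assisted-defecation item and as-needed enema and medication use by arm at each assessment, so that the size and direction of any shift can be seen.
- Amend the sentence in Statistical analyses that excludes supplementary analyses.
- Do not ask the blinded assessor to separate protocol DRS from other assistance. Eliciting that could reveal the allocation.

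The cost is one more derived variable and a few more table rows, with no added patients or visits. The downside is a sensitivity total that departs from the standard 8-item scale and cannot be compared directly with published totals; the full score is still reported for that purpose.
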